## Abstract

**Background:**

Peritoneal dialysis (PD)-related infections, such as peritonitis, exit site, and tunnel infections, substantially impair the sustainability of PD. Accordingly, PD-related infection is the top-priority research outcome for patients and caregivers. While PD nurse trainers teach patients to perform their own PD, PD training curricula are not standardized or informed by an evidentiary base and may offer a potential approach to prevent PD infections. The Targeted Education ApproaCH to improve Peritoneal Dialysis outcomes (TEACH-PD) trial evaluates whether a standardized training curriculum for PD nurse trainers and incident PD patients based on the International Society for Peritoneal Dialysis (ISPD) guidelines reduces PD-related infections compared to usual training practices.

**Methods:**

The TEACH-PD trial is a registry-based, pragmatic, open-label, multi-center, binational, cluster-randomized controlled trial. TEACH-PD will recruit adults aged 18 years or older who have not previously undergone PD training at 42 PD treatment units (clusters) in Australia and New Zealand (ANZ) between July 2019 and June 2023. Clusters will be randomized 1:1 to standardized TEACH-PD training curriculum or usual training practice. The primary trial outcome is the time to the first occurrence of any PD-related infection (exit site infection, tunnel infection, or peritonitis). The secondary trial outcomes are the individual components of the primary outcome, infection-associated catheter removal, transfer to hemodialysis (greater than 30 days and 180 days), quality of life, hospitalization, all-cause death, a composite of transfer to hemodialysis or all-cause death, and cost-effectiveness. Participants are followed for a minimum of 12 months with a targeted average follow-up period of 2 years. Participant and outcome data are collected from the ANZ Dialysis and Transplant Registry (ANZDATA) and the New Zealand Peritoneal Dialysis (NZPD) Registry. This protocol follows the Standard Protocol Items: Recommendations for Interventional Trials (SPIRIT) guidelines.

**Discussion:**

TEACH-PD is a registry-based, cluster-randomized pragmatic trial that aims to provide high-certainty evidence about whether an ISPD guideline-informed standardized PD training curriculum for PD nurse trainers and adult patients prevents PD-related infections.

**Trial registration:**

ClinicalTrials.gov NCT03816111. Registered on 24 January 2019.

**Supplementary Information:**

The online version contains supplementary material available at 10.1186/s13063-023-07715-0.

## Administrative Information

Note: the numbers in curly brackets in this protocol refer to a Standard Protocol Items: Recommendations for Interventional Trials (SPIRIT) checklist item numbers [1, 2]. The order of the items has been modified to group similar items (see http://www.equator-network.org/reporting-guidelines/spirit-2013-statement-defining-standard-protocol-items-for-clinical-trials/).

## Introduction

### Background and rationale {6a}

People with kidney failure require kidney replacement therapy for survival, which involves transplantation or dialysis, including hemodialysis (HD) or peritoneal dialysis (PD) [3]. Although patient survival is comparable between PD and HD in the first 3 years [4], PD is associated with a higher likelihood of returning to work, greater flexibility in dialysis schedules, cost savings from reduced travel to dialysis centers, better quality of life [5–7], patient satisfaction, ability to social distance, and independence [8]. PD is less expensive than HD in most countries and enables an increase in home-based dialysis therapies [4]. Despite these favorable features, the uptake of PD has diminished worldwide [9]. Estimates show that the percentages of prevalent patients with kidney failure who receive PD are below 10% in the USA, 22% in Canada, and 11% in Europe [10–13]. The prevalence of PD has decreased from 34% of the total dialysis population in Australia in 1995 to 18% in 2021 and from 61% of the New Zealand dialysis population in 1995 to 26% in 2021 [13].

Peritonitis causes PD cessation and death in 65% and 7% of patients on PD, respectively [13]. PD cessation causes patients to permanently transfer to HD or withdraw from treatment [14, 15]. PD-related peritonitis is also associated with peritoneal membrane dysfunction and higher morbidity, hospitalization, treatment costs, and mortality for up to 6 months after an episode [16]. The Standardized Outcomes in Nephrology – Peritoneal Dialysis (SONG-PD) initiative has identified PD-related infections as a core outcome for patients, caregivers, and clinicians for trials in patients on PD [14].

Substantial global variation in peritonitis rates exists among countries including Australia, France, New Zealand, Scotland, Taiwan, and the UK [17–20]. In addition, considerable variability exists in peritonitis rates between different PD units within the same country, with center-related factors outweighing patient-related factors [21]. PD is unique in that patients undertake their own treatment; thus, it is plausible that there could be a link between PD training and patient outcomes. Our publication following nationwide survey of PD units confirmed that differences in PD training practices currently exist in Australia [22]. It is hypothesized that a key center-related factor that may contribute to the variability in peritonitis risk is the variation in PD training [21, 23–25]. The ISPD has developed guidelines for PD training in clinical practice which are primarily based on adult education principles (andragogy) [26]. The ISPD guidelines provide recommendations concerning the performance of PD procedures, assisting patients to identify complications, and taking prompt, appropriate action [27, 28]. However, the effectiveness of standardized guideline-informed PD training curricula for trainers and patients has not been formally evaluated in a randomized controlled trial. A comprehensive PD training curriculum (TEACH-PD) for PD nurse trainers and patients has been developed by kidney nurses, doctors, educational experts and consumers, and, in alignment with the ISPD guidelines, utilizes evidence-based adult learning andragogy and eLearning pedagogy [29–31]. The curricula were identified as acceptable and usable by clinicians and patients in a feasibility study undertaken in two Australian units [30].

The Targeted Education ApproaCH to improve Peritoneal Dialysis outcomes (TEACH-PD) trial is a registry-based, pragmatic, multi-center, binational, cluster-randomized controlled trial (CRCT) to evaluate whether a guideline-informed standardized curricula of PD training for trainers and patients prevents PD-related infections and is cost-effective compared to standard care.

### Objectives {7}

The primary objective of the TEACH-PD trial is to determine whether the implementation of standardized training modules delays the time to the first episode of an exit site infection, tunnel infection, or PD-related peritonitis in incident PD patients compared to existing training practices.

The secondary objective is to determine whether a standardized PD training curriculum improves other important patient-centered outcomes and is cost-effective.

### Trial design {8}

The TEACH-PD trial is a pragmatic, multi-center, multinational, parallel arm, registry-based, CRCT, in which PD unit clusters are randomly assigned to implement TEACH-PD training curriculum or existing training practices for PD trainers and incident PD patients.

## Methods: Participants, interventions, and outcomes

### Study setting {9}

PD centers in Australia and New Zealand which provided PD training to more than ten patients over the 2 years prior to trial entry, as documented in the Australia and New Zealand Dialysis and Transplant (ANZDATA) Registry, are eligible. Clusters are randomly allocated to utilizing the TEACH-PD standardized curriculum or usual training practices for nurse trainers and incident PD patients. Allocation to treatment is stratified by site size according to the number of incident PD patients (small, medium, large, and very large). Investigators in Australia are asked to consider inclusivity regarding geography, unit size, location (including urban, regional, and rural), and center type (teaching and community hospitals). All 11 PD units in New Zealand have agreed to participate. The list of study sites is available elsewhere (see Additional file 1).

### Eligibility criteria {10}

To be eligible to participate in this trial, the participant must satisfy the following criteria:

Inclusion criteria:Patients new to PDPatients ≥ 18 years of ageNeed to undergo PD training (patients who have a caregiver to be trained will also be included in the trial)Are able to provide written informed consent

Exclusion criteria:Patients who are established on PD (i.e., prevalent patients) or those patients or caregivers with a history of previous exposure to PD training as an adult will be excluded as their learning requirements are expected to be different from incident PD patients.Paediatric patients are excluded as training modules were not designed or specifically tailored for their needs.

### Who will take informed consent? {26a}

TEACH-PD investigators will approach prospective trial participants to introduce the trial, describe the study, and answer questions. Prospective participants will be provided with the Patient Information Sheet and Consent Form. After discussing the trial, ample time will be given to the prospective participant to enquire about the trial and decide whether to participate. If the participant is unable to read the Patient Information Sheet and Consent Form, an impartial witness will be present during the entire discussion and will also be responsible for signing and dating the form on the participants’ behalf. In doing so, the witness attests that the information on the consent form was sufficiently and accurately explained to the participant, was understood by the participant, and that informed consent was freely given by the participant. If informed consent is provided, a consent form will be signed. The informed consent process covers the collection of study-related questionnaires and data linkage.

### Additional consent provisions for collection and use of participant data and biological specimens {26b}

The consent process includes a provision for data linkage to collect incidence of all cause hospitalizations with national and state-based health databases. No additional biological samples outside those collected as part of routine clinical care are being collected from participants.

## Intervention

### Explanation for the choice of comparators {6b}

Participating study sites in the experimental arm will implement PD training using TEACH-PD training curriculum/modules for the trainers and patients.

Participating study sites in the control group will continue pre-existing local PD training practice. A trial induction is completed at all control sites to assist with training in participant identification and screening, informed consent, data collection and entry, and outcome reporting.

### Intervention description {11a}

The TEACH-PD training curriculum and materials were developed by a core group of kidney nurses from The HOME Network (THN) [29, 30] in conjunction with senior medical clinicians from the Australasian Kidney Trials Network (AKTN), eLearning curriculum developers, consumer partners (i.e., patients and caregivers) and education experts, and were informed by the ISPD guidelines, utilizing evidence-based adult learning principles and best practice eLearning techniques [31]. A feasibility study was undertaken, involving ten PD trainers and 14 patients in two Australian PD units, to evaluate the feasibility and acceptability of the intervention, readability and usefulness of the education content and materials to nurse trainers and patients, and acceptability for participants [30]. The outcomes of this feasibility study informed the refinement of the TEACH-PD curriculum. As part of a process evaluation, 46 semi-structured interviews were conducted with PD nurse trainers and patients to ascertain their perspectives on the TEACH-PD intervention. These data were also used to refine the TEACH-PD curriculum intervention.

All PD nurse trainers at sites allocated to the TEACH-PD intervention will complete the following activities in the training framework [29] (Fig. 1: Training framework for PD nurse trainers):

**Fig. 1 Fig1:**
[figure not shown]
Training framework for PD nurse trainers

#### Induction visit

Induction is conducted either in-person or virtually at each cluster site to introduce the TEACH-PD curriculum and its learning outcomes, the modules, and the importance of standardization. The induction provides an overview of the patient training manuals, learning prerequisites, and assessment methods aligned to the learning outcomes. The trial induction also assists site staff with training in participant screening and enrolment, informed consent, data collection and entry, and outcome reporting.

#### Prerequisite knowledge

All nurse trainers are required to demonstrate nursing-level understanding of all clinical content areas covered by the PD patient training modules. This includes a combination of theory-based and practical knowledge assessments relevant to the PD training environment and the nurse trainer’s role.

#### Web-based training modules

In this step, the PD nurse trainers work through the TEACH-PD online modules. Competencies in the core topics in each module and clinical case studies are assessed using multiple-choice questions in an online learning management system interface (Blackboard) (Fig. 1: Training framework for PD nurse trainers).

#### Case study modules

On completion of the case studies, PD nurse trainers are assessed by developing a care plan and a lesson plan for PD patient training.

#### Practical “Train the Trainer” modules

The final assessment is based on the completion of the Nurse Competencies Checklist, which is completed in partnership with an accredited TEACH-PD nurse assessor as a record of having achieved all learning outcomes and competencies of the TEACH-PD curriculum. The checklist includes a list of practical competencies that are demonstrated during hands-on training within the PD training unit. The accredited assessors are kidney nurse consultants, nurse practitioners, and nurse educators.

Study sites allocated to the intervention arm implement the TEACH-PD training curriculum/modules for nurse trainers and patients once 75% of eligible PD nurse trainers have completed and achieved competency in the TEACH-PD training curriculum. PD nurse trainers conduct patient training at the hospital, clinic, or in the participants’ homes according to local policies.

All participants' follow-up and PD management will be in adherence with the TEACH-PD curriculum principles. Annual refresher training is offered to all intervention sites. Financial support will be provided to all intervention sites by reimbursement for the time spent on nurse module training and assessment and for the annual refresher training. In addition, the research team will also be providing technical support and assistance.

### Criteria for discontinuing or modifying allocated interventions {11b}

The TEACH-PD intervention will only be discontinued at the request of the participant.

### Strategies to improve adherence to interventions {11c}

PD trainers’ adherence to the TEACH-PD training modules will be assessed using the techniques outlined in the training framework for PD nurse trainers. The PD patient adherence will be assessed by their PD trainer.

### Relevant concomitant care permitted or prohibited during the trial {11d}

All aspects of care provided will follow standard local practice for individuals with kidney failure being managed by a nephrologist.

### Provisions for post-trial care {30}

There are no provisions for post-trial care given the anticipated low risk of harm from a participant’s involvement in this trial.

### Outcomes {12}

#### Primary outcome

The primary outcome is time from the first day of PD training to the first occurrence of any PD-related infection (PD peritonitis, tunnel infection, or exit site infection), as defined by ISPD guidelines [28].

#### Secondary outcomes

The secondary outcomes are the individual components of the primary outcome: PD infection-related catheter removal, transfer to hemodialysis for greater than 30 days and 180 days, all-cause hospitalization, PD infection-related hospitalization, death from any cause, and quality of life.

A cost-effectiveness analysis from the perspective of the health funder will be completed.

### Participant timeline {13}

The follow-up period for participants is a minimum of 12 months with a targeted average follow-up period of 2 years (Fig. 2: Trial schema showing an overview of the TEACH-PD trial). Reasons for participant early exit of trial outcomes are kidney transplantation, permanent transfer to hemodialysis, death, transfer to a PD unit not participating in the trial, loss to follow-up, withdrawal of participant consent, or at the patient’s or treating physician’s request.

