## Statistical methods

### Statistical methods for primary and secondary outcomes {20a}

Data will be analyzed at the patient level. Patient and treatment characteristics will be presented by study group using descriptive statistics. The primary outcome (coded as yes/no) and follow-up time (censored if < 24 months) will be displayed using Kaplan–Meier survival curves by group and by center size. Survival estimates of the treatment groups will be compared using the log-rank test for clustered data. Cox regression models with standard errors to allow for non-independent observations due to clustering will be used to assess the effect of the intervention on the primary and secondary outcomes. The models will be adjusted for cluster size category and country. The proportional-hazards assumption will be tested for each model. All data will be analyzed on an intention-to-treat basis with *p*-values less than 0.05 taken to indicate statistical significance.

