A key strength of the TEACH-PD trial is the utilization of a vigorous and adequately powered methodological approach to evaluate a standardized PD training curriculum for both trainers and patients. Both the approach and curriculum have been developed by patients, PD nurses (through THN) [29], doctors and education experts, and have been demonstrated as feasible and acceptable to clinicians and patients [30]. The TEACH-PD trial has a practical focus with broad eligibility criteria, avoidance of extra blood tests, use of local patient care practices, and minimal additional data collection, as data are collected via linkage with national and state-based administrative data and the ANZDATA and NZPD Registries. The registry-based design of the trial offers the advantage of rapid enrolment of eligible participants and complete (and potentially extended) follow-up of all study participants. The investigators acknowledge that PD nurses are the integral aspect of TEACH-PD and the key to its success, such that every effort has been made in designing this study to avoid excessive data collection and management burden. By following a pragmatic design with broad inclusion criteria, patient co-production, and involvement of clinical staff in the research design, the ability to implement the trial’s findings have been maximized [25].

Nonetheless, the TEACH-PD trial also has its limitations. First, it is an open-label trial and therefore potentially introduces detection and performance biases. Second, the trial is limited to PD centers in Australia and New Zealand, such that the findings may not be generalizable to other countries and income settings. TEACH-PD investigators acknowledge and have considered expanding the trial to international sites to improve external validity. Third, there exists a lag time between activation of control and intervention sites due to the time taken to complete the TEACH-PD training curriculum at intervention sites. However, the lengthy follow-up time for both arms will minimize any performance biases. Finally, training practices among sites in the control arm are heterogeneous and may increase outcome variation in the control arm, limiting comparability between arms. In addition, if a TEACH-PD patient from an intervention site is hospitalized and is assisted in their dialysis, this may be performed by a nurse who has not been trained in the TEACH-PD intervention.

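### One early-exit list governs all trial outcomes, so as written it also cuts off death, hospitalisation, quality of life and costs when a participant leaves PD or the unit

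*Protocol article*

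**What the plan says.** **Exit rule.** Participant timeline {13} states: "Reasons for participant early exit of trial outcomes are kidney transplantation, permanent transfer to hemodialysis, death, transfer to a PD unit not participating". The sentence goes on to loss to follow-up, withdrawal of consent, and a request by the patient or the treating physician. Nothing in it separates one outcome from another. The same section sets the horizon: "The follow-up period for participants is a minimum of 12 months with a targeted average follow-up period of 2 years".

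**Outcomes it covers.** Besides the infection components and catheter removal, Secondary outcomes lists "transfer to hemodialysis for greater than 30 days and 180 days, all-cause hospitalization, PD infection-related hospitalization, death from any cause, and quality of life" and adds: "A cost-effectiveness analysis from the perspective of the health funder will be completed". The Abstract (Methods) also names "a composite of transfer to hemodialysis or all-cause death".

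**Data sources.** Adverse event reporting and harms {22} takes deaths from the renal registries and all-cause hospital stays from data linkage. Healthcare utilization takes resource use from national and state databases. The two consent sections ({26a}, {26b}) already cover linkage.

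**Other statements on follow-up.** The retention section {18b} stops data collection expressly only for participants who withdraw. Statistical methods {20a} says "All data will be analyzed on an intention-to-treat basis". The Discussion presents "complete (and potentially extended) follow-up of all study participants" as an advantage of the registry-based design.

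**The concern.** Someone who stops PD is no longer at risk of a PD infection, so ending follow-up there is reasonable for the primary outcome, its components and infection-related catheter removal. The same person can still die, be admitted to hospital, have a quality of life and incur costs. An exit list applied to all trial outcomes would remove those events and costs by rule.

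The exits are not incidental. Background and rationale {6a} says that peritonitis causes PD cessation, that cessation leads to permanent haemodialysis or withdrawal from treatment, and that peritonitis is associated with more hospitalisation, cost and mortality for up to 6 months. It also says that PD costs less than haemodialysis in most countries. If training prevents infection, permanent transfers could differ between arms, and some of the deaths and costs of interest could come after them. Censoring at transfer would then be informative for death and hospitalisation, and the funder-perspective analysis could omit time on haemodialysis, a consequence of infection that the trial hopes to avoid.

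**Working it through.** **1. The plan's own figure.** Inputs from Sample size {14}: hazard ratio 0.80, 80% power, 5% error (taken as two-sided), cluster size 37, intra-cluster correlation 0.001, 53% of controls infection-free.
- Design effect: 1 + (37 − 1) × 0.001 = 1.036.
- Events: 631 (Schoenfeld) × 1.036 = 654, or 636 (Freedman) × 1.036 = 659. The plan states about 650.
- Event share: control 0.47; intervention 1 − 0.53^0.8 = 0.398; mean 0.434.
- Participants: 654 / 0.434 ≈ 1506 (Schoenfeld) or 1518 (Freedman). The plan states about 1500.

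The figures reproduce, and the point does not touch them.

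**2. The statements side by side.**

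| Section | What it implies for someone who leaves PD or the unit, without withdrawing |
|---|---|
| Participant timeline {13} | exits trial outcomes |
| Retention {18b} | no stop to data collection (the stop is for withdrawal only) |
| Harms {22}, Healthcare utilization | deaths, admissions and resource use come from sources not described as limited to PD or to trial units |
| Discussion | follow-up is complete for everyone |

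The first row and the last cannot both hold for death, hospitalisation and cost.

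**3. How many deaths could fall after exit.** The documents give no death, transfer, transplant or unit-move rate, so every rate here is assumed: constant death rate d, constant combined exit rate x, T = 2 years, 1500 participants.
- Deaths before exit: d/(d + x) × (1 − exp(−(d + x)T))
- All deaths, if the death rate is the same after exit: 1 − exp(−dT)
- Share after exit: 1 minus the ratio of the two.

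Worked case, d = 0.12 and x = 0.20: before exit 0.375 × (1 − exp(−0.64)) = 0.177, or 266 deaths; all deaths 1 − exp(−0.24) = 0.213, or 320. Share after exit: 17%.

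| d | x | All deaths | Before exit | After exit |
|---|---|---|---|---|
| 0.08 | 0.10 | 222 | 202 | 9% |
| 0.08 | 0.40 | 222 | 154 | 30% |
| 0.12 | 0.10 | 320 | 291 | 9% |
| 0.12 | 0.40 | 320 | 224 | 30% |

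**4. Sensitivity.** If the death rate doubles after exit, write a = d + x. All deaths become 1 − exp(−aT) − x[exp(−2dT) − exp(−aT)]/(a − 2d), and the share after exit is 15% to 45%. At T = 1 year the range across both assumptions is 5% to 29%.

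These are shares of deaths in the two arms together. They do not give a bias in the treatment comparison, which would need exit and death rates by arm.

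**The case against.** The strongest reply is that this is wording, not a design failure. Several parts of it stand.

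- **Data loss is not stated.** A reader might infer that deaths and admissions after exit will certainly be discarded. The article never says that registry or linkage extraction stops at exit, and {18b} ties the stop to withdrawal. What stands is that the exit sentence, read plainly, says otherwise.
- **A condensed article may leave outcome-specific censoring to fuller documents.** True, and the absence of such a table is not the complaint. The complaint is a rule that the article does state, without qualification.
- **The 30-day and 180-day haemodialysis outcomes.** A reader might infer a flat contradiction. It arises only if exit is dated at the switch. If permanence is established after the window has passed, there is none. The article does not define it.
- **The composite.** Permanent transfer is itself an event there, so exit at transfer costs it little. Only transplant, unit moves and requests matter.
- **Intention-to-treat.** The statement in {20a} can mean analysis by allocated arm, which censoring does not breach. The clear conflict is with the Discussion.
- **Bias toward no effect.** This is a plausible guess, but no figure in the documents supports a direction.
- **Uncosted haemodialysis time.** With an assumed transfer rate of 0.15 per year, 2 − (1 − exp(−0.30))/0.15 = 0.272 years each, or 408 patient-years in 1500 participants. That lets nobody die; an assumed death rate of 0.10 per year lowers it to about 358. It also pools the arms. If all transfer fell by 20% (0.15 to 0.12), the difference would be 0.050 × 750, about 38 patient-years, or about 33 with deaths. The total should not be read as the error in the economic comparison.
- **Sources.** Nothing shows that the New Zealand PD registry follows people after PD ends, and haemodialysis cost data are not named. The remedy should not rely on either.

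**Conclusion.** The concern holds for all-cause death, all-cause hospitalisation, quality of life and cost-effectiveness, and for the composite after transplant or a unit move. For these, the exit list as written truncates follow-up at post-randomisation events, risks informative censoring, and cannot be squared with the follow-up claimed in the Discussion. It does not hold against the infection outcomes or the sample size.

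The only size that can be offered is conditional: about 9% to 30% of deaths after exit over 2 years, on assumed constant rates and unchanged mortality after exit. The documents support neither a direction nor a size for bias between arms, and they do not establish that the data will in fact be dropped. They support two incompatible follow-up rules, which could give different secondary and economic results. The choice should be fixed before analysis.

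**What to change.** 1. Limit the exit list in Participant timeline {13} to PD-specific outcomes: the infections and infection-related catheter removal.
2. For death, all-cause hospitalisation, resource use and costs, and the haemodialysis-or-death composite (after transplant or a unit move), continue to a common close-out date through ANZDATA and data linkage, whatever the modality or unit, unless consent to data use is withdrawn.
3. State how permanent transfer is dated, so that the 30-day and 180-day haemodialysis outcomes stay observable.
4. Quality of life comes from questionnaires, which the registries cannot replace. State whether they continue after exit and, if not, how the quality-adjusted life years are handled.
5. Reconcile the exit list with the retention section {18b} and the Discussion.

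The cost is protocol and analysis-plan wording, plus some extra extraction and linkage under consent that already covers linkage. Continuing questionnaires, if chosen, would add site or e-mail contact. The primary outcome's PD-cessation rule, the event target and the number of participants stay as they are.
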